### Intervention group: E-Fit

E-Fit targets multiple EF domains, focusing on four that have been identified as being impaired by two meta-analyses on EF in children with CHD: inhibition, planning, flexibility and working memory.^4 5^ See online supplemental file 4 for details. These are addressed in a multimodal approach consisting of three personalised and adaptive elements: (1) computerised training played alone, (2) remote 1:1 strategy coaching with the child and a psychologist and (3) analogue board and card games fostering EF abilities that can be played alone or with friends and family (online supplemental table S3). The intervention lasts for 8 weeks.

10.1136/bmjopen-2023-073345.supp4Supplementary data

#### Computerised training

Participants use the platform CogniFit Inc 2022 (CogniFit) for the computerised training. CogniFit was selected based on literature^52 53^ and its successful use in other similarly aged populations^54^ and because it targets several EF domains. This is in contrast to Cogmed, which only targets working memory. From the CogniFit platform, 11 games targeting the aforementioned EF domains were selected, considering 3 games per function (online supplemental table S4). These games involve tasks that require information retention and manipulation, strategy development and task switching.^55^ These games are adaptive to the child’s level of performance. Participants play the assigned games at home on a computer, smartphone or tablet. A device is provided if needed. The child is asked to play three times a week for 20 min over the course of the 8-week intervention period.

#### Strategy coaching

The strategy coaching is conducted remotely. A psychologist is assigned to each family as a coach to monitor and support them throughout the intervention. The child meets with the coach once a week for 60 min for a total of eight sessions.

The first session discusses baseline assessment results and the child’s strengths and weaknesses.^56^ Further, the first module of CogniFit is performed to make sure the child understands how to use CogniFit. In this session, a parent participates with the child.

For the six following sessions, parents fill in a short questionnaire^47^ to identify EF domains in which their child faces difficulties. Of 11 EF domains rated, the 6 indicating the most difficulties are selected for the coaching sessions. Each of these six sessions has standardised guidelines and start with a story about an EF and an explanation of how this function engages our brain.^44–46 48^ Afterwards, the child completes a task teaching a strategy for the EF in question^47^ (for more details, see online supplemental file 4). During the coaching sessions, solutions to difficulties with adhering to E-Fit are suggested.

The eighth and final coaching session consists of the wrap-up and outlook, where a parent again participates with the child.^57^

Additionally, the coach calls the parents in the first and fourth week to discuss the upcoming sessions that will be conducted with the child only. Parents can suggest specific situations to be addressed in the subsequent strategy coaching. In response, the coach provides tips on how parents can support their child with the respective EF.^47^ For an overview of the strategy coaching procedure, see table 2.

**Table 2 T2:** Strategy coaching procedure

	Week 1	Week 2	Week 3	Week 4	Week 5	Week 6	Week 7	Week 8
Child		60 min individual topic	60 min individual topic	60 min individual topic	60 min individual topic	60 min individual topic	60 min individual topic	
Parent	30 min call			30 min call				
Parent and child	60 min initialisation session							45 min wrap up session

Following the manual, the strategy coaching teaches strategies to promote EF in everyday life.^47^ A clinical neuropsychologist reviewed the strategy coaching, and the manual is available in German language.

#### Analogue training

Thirteen board and card games are provided to the families (online supplemental table S5). They are suited for this age group and target EF abilities. A special needs and trained game educator helped select the games targeting the above-mentioned EF domains for children between 10 and 12 years of age. Like the computerised training, the analogue training also demands a range of diverse functions, including rule retention, flexible adaptation to other players, impulse control and strategic thinking. Often, a single game may require multiple functions simultaneously. Families are free to play as much as they want but are asked to report the date, duration and name of the analogue games played.

### Control group

The control group receives standard of care, including cardiac surveillance, neurodevelopmental counselling and therapies such as speech- and physiotherapy. Because the control group families know the scope of the tested intervention, this may lead to contamination: during the trial, parents of control children may engage their children in activities used in the intervention fostering EF. To detect this and where occurring, to measure the time spent on it, parents and children complete an electronic diary four times a week for 8 weeks to monitor the child’s everyday activities (online supplemental file 5 and online supplemental table S3). After the final visit at the end of study participation, the control group families receive the list of EF-enhancing analogue games used, EF fact sheets and a 2-month CogniFit login.

10.1136/bmjopen-2023-073345.supp5Supplementary data

### Primary outcome measures

The feasibility of the E-Fit intervention will be measured in six areas, as described by Bowen *et al*.^58^ Except for Practicality and Limited efficacy, primary outcome measures will be collected only in the intervention group throughout the intervention period. For a summary of measures and assessment time points, see table 3. The following areas will be assessed.

**Table 3 T3:** Feasibility focus areas and assessment tools

Area of focus	Assessment tool	Group	Time point	Completed by
Acceptability	Acceptance and Feasibility Scale^32^	E-Fit	Final coaching	Parents and children
	Children’s Feeling Scale^73^	E-Fit	Intervention period, before and after each online training	Children
	Observed engagement^74^	E-Fit	Each coaching session	Coach
Demand	Acceptance and Feasibility Scale^32^	E-Fit	Final coaching	Parents and children
	Fun and Demand^75^	E-Fit	Intervention period, before and after each online training	Children
	Session data: duration, no of completed sessions and for the computerised training, the coaching and the card games	E-Fit	Intervention period	
	Recruitment rate	E-Fit	End of study	
Implementation	E-Fit Fidelity Measurement System tool, developed based on Feely *et al*^59^	E-Fit	End of study	Two separate raters
Practicality	Acceptance and Feasibility Scale^32^	E-Fit	Final coaching	Parents and children
	Feedback in coaching sessions	E-Fit	Each coaching session	Parents and children
	Observed involvement^74^	E-Fit	End of study	
	Session rating scale^76^	E-Fit	Each coaching session	Children
	Observed engagement^74^	E-Fit	Each coaching session	Coaches
	Recruitment rates	Both	End of study	
	Retention rates	Both	End of study	
	Completion of weekly sessions	E-Fit	End of study	
	No of adverse events	Both	Continuously	
Integration	Acceptance and Feasibility Scale	E-Fit	Final coaching	Parents and children
Limited efficacy	Delis-Kaplan Executive Function System^70^	Both	BL, T_1_, T_2_	
	Wechsler Intelligence Scale for Children- fifth edition^66^	Both	BL, T_1_, T_2_	
	Test of Attentional Performance^71^	Both	BL, T_1_, T_2_	
	Balloon Analogue Risk Task^77^	Both	BL, T_1_, T_2_	
	Behaviour Rating Inventory for Executive Function	Both	BL, T_1_, T_2_	Parents* and teachers

*If possible, completed by both parents separately.

E-Fit, executive function intervention.

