### Aims and hypotheses

This study aims to test the feasibility of a multimodal personalised EF intervention for children with complex CHD and EF impairments. To evaluate E-Fit’s feasibility, the following aims and hypotheses will be explored:

Aim 1: Assess whether children with CHD and EF impairments can adhere to E-Fit.

Hypothesis 1: Study participants will complete at least 80% of the strategy coaching and computerised training sessions of E-Fit.

Aim 2: Assess the acceptability of E-Fit for children with CHD and EF impairments and their parents.

Hypothesis 2: Study participants and their parents will indicate high acceptability of E-Fit as measured by average ratings of 3 or higher on a 4-point rating scale assessing the acceptability of each programme component.

Aim 3: Assess the feasibility of E-Fit for children with CHD and EF impairments and their parents.

Hypothesis 3: Study participants and their parents will indicate high feasibility of E-Fit as measured by average ratings of 3 or higher on a 4-point rating scale assessing the user-friendliness and ease of integrating each programme component into their daily lives and environments.

Aim 4 (exploratory): Measure the impact of E-Fit on improving EF skills in children with CHD and EF impairments.

Hypothesis 4: We anticipate a moderate effect in the direction of improved EF from preintervention to postintervention in study participants.

The rationale for projection numbers provided in the hypotheses is as follows:

Adherence of 80% is based on previous intervention studies.^21^

The decision to use rating scale ratings of 3 or higher is founded on the 4-point rating scale (1=do not agree at all, 4=fully agree). Therefore, 3 and above are considered affirmative.

Effect sizes are based on the results of a meta-analysis. Specifically, a value of 0.38 pertains to explicit EF practice (including computerised and analogue training across all populations), while 0.46 corresponds to strategy coaching across all populations.^23^

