#### Integration

Integration assesses the extent to which the intervention can be integrated within the existing system. This addresses the perceived fit with infrastructure and perceived sustainability during the last coaching session.

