### Data analysis plan

The feasibility of the intervention will be delineated from the descriptive statistics.

Descriptive statistics will be calculated, including means, SD, medians and IQRs for continuous variables and frequency counts and percentages for categorical variables. The newly developed E-Fit Fidelity Measurement System will be evaluated. Two raters will complete it individually, and inter-rater reliability will be reported. To report limited efficacy, within-subject differences between EF performances from baseline to post-treatment and 6-month follow-up assessments are to be investigated across treatment groups with an intention-to-treat analysis. Linear regression controlling for covariates, involving differences in means and 95% CI, will be used to assess differences between groups and time points for continuous outcomes. Proportions and logistic regressions for binary outcomes will be used to examine group effects (eg, comparison of clinically relevant vs not clinically relevant scores in the BRIEF, χ^2^ tests, ORs and 95% CI). Given that missing values are missing at random, they will be imputed using multiple imputations.

The data will be visually inspected to identify discordant and influential observations. All analyses will be conducted with an alpha level of 0.05. The statistical software R will be used for all analyses.^50^ The final project report will describe and justify any deviations from the original statistical plan.

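### The scale that appears to decide Hypotheses 2 and 3 is collected only at the last coaching session, so the 3-or-higher average is judged on families who completed E-Fit

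*Protocol article*

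**What the plan says.** In the protocol article, Table 3 (Primary outcome measures) enters the "Acceptance and Feasibility Scale" under acceptability, demand, practicality and integration. In all four rows it is completed in the E-Fit arm by parents and children, at "Final coaching". The Integration paragraph gives the same timing: "This addresses the perceived fit with infrastructure and perceived sustainability during the last coaching session". The Strategy coaching section places that session at the end of the programme: "The eighth and final coaching session consists of the wrap-up and outlook, where a parent again participates with the child". Table 2 puts it in week 8. The article lists no collection of this scale at withdrawal.

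Under Aims and hypotheses, Hypothesis 2 needs "average ratings of 3 or higher on a 4-point rating scale assessing the acceptability of each programme component". Hypothesis 3 needs "average ratings of 3 or higher on a 4-point rating scale assessing the user-friendliness and ease of integrating each programme component". The anchors are "1=do not agree at all, 4=fully agree", and 3 or above is treated as affirmative.

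The Data analysis plan reads feasibility from descriptive statistics. It mentions intention-to-treat only for limited efficacy. After the regression models it adds: "Given that missing values are missing at random, they will be imputed using multiple imputations".

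**The concern.** A family that finds E-Fit unattractive, or cannot fit it into the week, is less likely than others to reach session 8. The quantity being measured is thus a plausible cause of its own missingness. If only families who reach the end are rated, the average describes them and not all those allocated to E-Fit, and the probable direction of error is towards meeting the threshold.

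Hypotheses 2 and 3 are two of the three non-exploratory hypotheses. The Ethics and dissemination section says the pilot data will inform whether a definitive trial follows.

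**Working it through.** **Which scale.** Aims and hypotheses does not name the instrument. The other Table 3 entries on related topics are the Children's Feeling Scale, Fun and Demand and the session rating scale (children only), observed engagement (coach), and feedback in coaching sessions (parents and children, but not listed as a rating scale). Only the Acceptance and Feasibility Scale is a rating scale completed by both parents and children. The link to Hypotheses 2 and 3 is an inference, but a strong one.

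**The plan's own figures** (Sample size determination). 60 × 0.75 = 45 enrolled and 45 × 0.90 = 40.5, stated as 40, or 20 per arm. The step before gives 210 × 0.30 = 63 against a stated 60, which is rounding of approximate figures. Ten per cent of 20 is 2 families.

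**Effect of missing raters.** Let f be the share of E-Fit families with no rating, C the completer mean and S the mean that those who stopped would have given.

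- All-allocated mean = (1 − f) × C + f × S
- Completer mean needed for an all-allocated mean of 3.0 = (3 − f × S) / (1 − f)

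The documents give no value for S. I assume 1 to 2, the two non-affirmative points on the scale, and vary f around the stated 10%.

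| No rating | f | All-allocated mean if C = 3.0 (S = 1 / S = 2) | C needed for 3.0 overall (S = 1 / S = 2) |
|---|---|---|---|
| 1 of 20 | 0.05 | 2.90 / 2.95 | 3.11 / 3.05 |
| 2 of 20 | 0.10 | 2.80 / 2.90 | 3.22 / 3.11 |
| 4 of 20 | 0.20 | 2.60 / 2.80 | 3.50 / 3.25 |

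Worked line for 2 of 20: (3 − 0.10 × 1) / 0.90 = 3.22 and (3 − 0.10 × 2) / 0.90 = 3.11.

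The 20 per arm can also be read as already net of drop-out. With 2 lost of 22 the needed completer mean is 3.20 / 3.10, and with 3 lost of 23 it is 3.30 / 3.15. The message is the same.

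**How close to 3 it has to be.** With 2 of 20 missing, a completer mean of 3.1 gives 2.89 / 2.99 over all allocated, below the threshold. A completer mean of 3.3 gives 3.07 / 3.17, above it.

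**Whether the analysis repairs it.** Descriptive statistics on the observed ratings give the completer mean. If the imputation sentence were applied to these ratings, no family that stopped early would have a value on the scale, so the imputation model would have to be fitted to completers. Per-session data could improve that model somewhat. It would still rest on missing at random, which is doubtful when low acceptability itself drives stopping.

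**The case against.** Early stopping is not invisible. Table 3 also lists session data, completion of weekly sessions and retention, and Hypothesis 1 has its own 80% completion criterion. Children's ratings around each online training, and the session rating scale, family feedback and observed engagement at each coaching session, exist up to the point where a family stops. All of this informs the feasibility conclusion. It stands as a limit on the consequence, but none of it enters the 3-or-higher average.

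The size is illustrative. It depends on assumed ratings, and the article does not say whether the 10% loss falls before session 8 or equally by arm. That also stands.

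An exit questionnaire could be described in a full protocol not shown here. However, the single time point is a schedule that the article states, in four rows and again in the text, and not a detail it leaves open.

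Three stronger readings are tempting and are not supported:

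- A reader might infer that multiple imputation is the plan's remedy for these ratings. The sentence follows the efficacy models, while feasibility is assigned to descriptive statistics. Its scope is at most unclear.
- A reader might infer that the coach is present when the scale is filled in, which would invite favourable answers. The entry is a time point. No mode of administration is given, and coaching is remote.
- A reader might infer that the threshold is a formal go/no-go gate. The article says only that pilot data inform the decision, and feasibility is judged over six areas.

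**Conclusion.** The point holds as a design weakness that is cheap to remove. As scheduled, the average behind Hypotheses 2 and 3 covers only families who reach session 8, and it probably overstates acceptability and feasibility among all allocated to E-Fit. At about 10% missing, with those who stopped assumed to rate 1 to 2, a completer mean of 3.0 overstates the all-allocated mean by 0.10 to 0.20. A completer mean from 3.00 up to about 3.11 to 3.22 would pass while the all-allocated mean fails. Well above that range the conclusion would not change.

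This rests on two things the documents do not give: the identity of the scale behind the two hypotheses, which is inferred, and the ratings of families who stop early, which are assumed.

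**What to change.** - **Collection.** Obtain the scale from every family randomised to E-Fit at the existing 2-month assessment, and at withdrawal from those who stop early. REDCap is already in use, so a survey link would serve. It should be answered away from the test session, so that the blinded assessor does not learn the allocation.
- **Reporting.** For Hypotheses 2 and 3, give the number of raters out of all allocated to E-Fit, for parents and children separately.
- **Sensitivity result.** Repeat both hypotheses with missing ratings counted as not affirmative. For the average, this can be shown with missing values set to 2 and then to 1.
- **Table 3.** Amend the four rows to the new time points.

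The cost is a table edit, a survey link, a small reminder effort for families who withdrew, and possibly slightly less favourable ratings. If collection has already ended, the reporting and sensitivity steps can still be done.

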#### Acceptability

Acceptability examines suitability, satisfaction and attractiveness to programme deliverers and recipients. It is measured by questions about satisfaction, intent to continue use and perceived appropriateness throughout the intervention period.

#### Demand

Demand is assessed by the extent to which the intervention is likely to be used or how much demand exists. This includes measures for the fit within the family, perceived positive or negative effects on the family, actual use, expressed interest or intention to use, and perceived demand throughout the intervention period.

#### Implementation

To ensure the successful delivery of the intervention to participants, implementation is a critical aspect. The E-Fit Fidelity Measurement System was newly developed following existing guidelines.^59^ The purpose of this system is to measure the degree of fidelity with which the newly developed E-Fit was implemented. Essential components, including specific questions to be asked and required session completion, were organised, phrased and complemented by response choices (yes and no). During the study, the Fidelity Measurement System will be piloted and evaluated.

#### Practicality

Practicality explores how an intervention can be delivered to intended participants with existing means, resources and circumstances. It includes factors affecting implementation ease or difficulty, efficiency, speed and quality of implementation, positive or negative effects on target participants, and the participant’s ability to complete the intervention activities throughout the intervention period.

#### Integration

Integration assesses the extent to which the intervention can be integrated within the existing system. This addresses the perceived fit with infrastructure and perceived sustainability during the last coaching session.

#### Limited efficacy

Limited efficacy explores whether the new intervention shows promise of succeeding with the intended population. This is measured by evaluating the programme’s intended effects or process on key intermediate variables, effect-size estimation and maintenance of changes from initial change (see table 1 for an overview of EF measures).

### Secondary outcome measures

In addition to primary outcome measures, we will examine other variables assessing the success of the intervention. The following secondary outcome measures are to be collected from both groups at baseline, 2-month and 6-month follow-up: The Family Relationship Index is a self-report measure used to evaluate subjective quality of family environment for parents.^60^ The Kidscreen-10 assesses the child’s subjective health and well-being, and the Kidscreen-27 assesses the child’s health and well-being from a parent’s perspective; these are combined to assess the child’s QoL.^61^ The parents will complete the short form of the Conners-3 and the Social Responsiveness Scale^62 63^ to screen for behavioural problems. The Resilience Scale (RS-13) is a self-reported questionnaire assessing resilience by acceptance of self-competencies, life competencies and personal competencies. This questionnaire will be completed by the parents and the child.^64^

### Covariate measures

Medical, sociodemographic and patient-specific factors and IQ will be measured in both groups at baseline and be treated as covariates for the effectiveness of the intervention and to describe the population who participated in the intervention.

SES will be estimated on a six-point scale for both paternal and maternal education, leading to the lowest possible SES sum score of 2 and the highest of 12.^65^ Cardiac and neonatal data will be collected from medical records. A short form of the Wechsler Intelligence Scale for Children, fifth edition, will be used to assess total IQ once at the baseline assessment.^66^

### Data analysis plan

The feasibility of the intervention will be delineated from the descriptive statistics.

Descriptive statistics will be calculated, including means, SD, medians and IQRs for continuous variables and frequency counts and percentages for categorical variables. The newly developed E-Fit Fidelity Measurement System will be evaluated. Two raters will complete it individually, and inter-rater reliability will be reported. To report limited efficacy, within-subject differences between EF performances from baseline to post-treatment and 6-month follow-up assessments are to be investigated across treatment groups with an intention-to-treat analysis. Linear regression controlling for covariates, involving differences in means and 95% CI, will be used to assess differences between groups and time points for continuous outcomes. Proportions and logistic regressions for binary outcomes will be used to examine group effects (eg, comparison of clinically relevant vs not clinically relevant scores in the BRIEF, χ^2^ tests, ORs and 95% CI). Given that missing values are missing at random, they will be imputed using multiple imputations.

The data will be visually inspected to identify discordant and influential observations. All analyses will be conducted with an alpha level of 0.05. The statistical software R will be used for all analyses.^50^ The final project report will describe and justify any deviations from the original statistical plan.

